#### Randomization and blinding

2.2.3.

Eligible participants will be recruited at each institution (the mental health service of each hospital that agreed to take part in the study in Portugal) through telephone contact by the researchers in collaboration with the multidisciplinary team. The study will also be publicized in the media so that older adults can contact the researchers if they are interested in participating. A baseline assessment will be carried out and all instruments will be applied after informed consent from participants. All participants who agree to participate in the study will be assigned a code and will be randomly assigned to either MCT-Silver (experimental group where the intervention will be applied) or the control group (no stratification factors). This randomization will be performed using a computer program. The control group will not be administered the intervention (MCT-Silver). In both groups, treatment will be maintained as usual (Treatment As Usual – TAU) and participation in other interventions as well as use of medications will be carefully monitored. Study participants will be informed that they should not reveal which group they are in and will be reminded of this at each testing session. All participants will be re-assessed at the end of the intervention and 3 months after completion, with the application of all planned instruments. Assessments will be performed by the same rater before and after the intervention and at follow-up. Assessors will be trained in the administration of all instruments prior to the start of the study. A third researcher will inform patients of group assignment so that raters will remain blinded throughout the study. The Side Effects of Intervention questionnaire and patient satisfaction with MCT-Silver will be applied to the experimental group post-intervention (Table 1; Figure 1).

**Table 1 tab1:** Study schedule.

	Study period				
	Enrolment	Randomization	Intervention (8 weekly sessions)	Post (8 weeks)	Follow-up (3 months)
TIMEPOINT	T-1	T0		T1	T2
Enrolment:					
*Eligibility screen*	X				
*Informed consent*		X			
*Randomization*		X			
Interventions:					
*Treatment As Usual (TAU)*	X	X	X	X	X
*MCT-Silver*			X		
Assessments: *Baseline*		X			
*Post-intevention*				X	
*Follow up*					X

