#### Participants

2.2.2.

The sample will be selected by a probabilistic method and participants will be randomly assigned to one of two groups (MCT-Silver vs. TAU) based on a randomized plan.

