#### Data analysis

2.2.9.

The data will be analysed using Statistical Package for Social Sciences software (SPSS®) version 24.0 for Windows. Descriptive analysis will be used to characterize the sample. Within-group differences (t0 to t1 and t0 to t2) will be examined using paired sample *t*-tests. To evaluate change in primary and secondary outcomes between the two groups, we will perform ANCOVAs with treatment as the between-subject factor (MCT-Silver + TAU vs. TAU), the difference score of the outcomes (t1 – t0 and t2 – t0, respectively) as the dependent variable, and the baseline score of the respective outcome as the covariate. We chose ANCOVAs with difference scores instead of a repeated measures ANOVA to avoid regression to the mean and to control for potential baseline differences.

Intention-to-treat (ITT) analyses (including all participants who provided baseline data) using multiple imputation (MI) will be conducted. Analyses utilizing a complete cases sample (CC; including only complete data—i.e., baseline, post, and follow-up) will also be conducted. We will use analogous models to assess changes (t0-t1; t0-t2) for the secondary outcomes (WHOQOL-BREF item 1, DAS-18B, ERR-10-A, AAQ12, MCQ-30, MADRS, PHQ-9, RSE). We will also conduct planned moderation analyses for the primary outcome at post-assessment (BDI-II). Demographic characteristics (age, sex, education) and clinical characteristics (previous or current treatment, comorbid anxiety disorder, number of sessions attended) as well as baseline scores on secondary outcomes (WHOQOL-BREF item 1, DAS-18B, ERR-10-A, AAQ12, MCQ-30, MADRS, BDI, RSE) will be examined separately using moderation models as defined as defined by the PROCESS SPSS macro (model 1) [59]. Self-rated depression difference scores (t0–t1 and t0–t2) will be entered as the dependent variable (Y) and depression severity at t0 as the covariate.

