### Validity and reliability/rigour

2.4.

Variables such as educational level, duration of mental disorder, and type of treatment may influence the results of this study. The proposal to use the stratified random sampling method in this study aims to minimize confounding bias. All procedures, including the implementation of the intervention will be carried out after trainers have completed MCT-Silver training to minimize the risk of bias. Participants will be randomly allocated to either the experimental group [MCT-Silver + Treatment As Usual (TAU)] or the control group (TAU only). A computer-generated stratified random sampling method will be applied taking into consideration an equitable distribution by sex and age to promote sex and age equality and inclusiveness. Finally, all raters will be blinded to participant group assignment.

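### Allocation is described as having no stratification factors in section 2.2.3 and as stratified by sex and age in section 2.4; if the second holds, the ANCOVA leaves the strata out

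*Protocol article*

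**What the plan says.** Four parts of the protocol article bear on this.

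- **Section 2.2.2 (Participants):** "The sample will be selected by a probabilistic method and participants will be randomly assigned to one of two groups". No factors are named.
- **Section 2.2.3 (Randomization and blinding):** a computer program assigns participants to MCT-Silver "or the control group (no stratification factors". The same section describes recruitment: telephone contact through the participating hospitals, and "The study will also be publicized in the media so that older adults can contact the researchers if they are interested in participating".
- **Section 2.4 (Validity and reliability/rigour):** "The proposal to use the stratified random sampling method in this study aims to minimize confounding bias". Later in the same paragraph come "Participants will be randomly allocated to either the experimental group" and, as the next sentence, "A computer-generated stratified random sampling method will be applied taking into consideration an equitable distribution by sex and age".
- **Section 2.2.9 (Data analysis):** "we will perform ANCOVAs with treatment as the between-subject factor", the change score as dependent variable and "the baseline score of the respective outcome as the covariate". Age and sex appear only among the candidate moderators of the BDI-II result, each examined in a separate model.

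**The concern.** The allocation method is a basic element of a randomised trial, and here it has two descriptions that exclude each other. Whoever sets up the randomisation program cannot follow both, and a reader of the results could not tell which was used.

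The consequence depends on which section is right. If there are no strata, section 2.4 claims a protection against imbalance by sex and age that the design does not provide. If there are strata, the analysis ignores a restriction placed on the allocation. The usual variance estimate then includes between-stratum variation that the balanced allocation has already removed from the treatment comparison. The result is a standard error that is too large and some lost power.

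**Working it through.** **Comparing the texts**

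1. Section 2.2.3 excludes stratification factors outright. Section 2.4 names two, sex and age. As descriptions of allocation they are incompatible.
2. Could section 2.4 mean selection of the sample? Its wording is that of sampling. But the sentence just before concerns assignment to the two arms, and the stated purpose, limiting confounding, is served by allocation. Recruitment through hospital contacts and self-referral is not a stratified random sample either. Taken literally, section 2.4 would conflict with the recruitment text instead, so one statement is wrong on either reading.
3. Section 2.4 names educational level, duration of disorder and type of treatment as variables that may influence the results, then balances on sex and age. Its rationale and its factors do not match.
4. The main ANCOVA contains treatment and the baseline score of the outcome. Neither sex nor age is in it.

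**Size of the effect if section 2.4 governs**

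The plan has no figure to reproduce: section 2.2.4 defers the trial's sample size, significance level and power until after the pilot. The following is therefore an illustration.

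Assumed inputs:
- two-sided nominal alpha 0.05 (critical value 1.960);
- 80% power for the ANCOVA that includes the strata (0.842 added, so an expected test statistic of 2.802);
- exact balance within strata and a large-sample normal approximation;
- R², the share of residual variance after the baseline score that sex and age explain.

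Formulas:
- ratio of reported to true standard error = 1/√(1 − R²)
- true type I error = 2[1 − Φ(1.960/√(1 − R²))]
- power without the strata = Φ(2.802 − 1.960/√(1 − R²))

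Worked for R² = 0.05: 1/√0.95 = 1.026, and 1.960 × 1.026 = 2.011. Type I error = 2[1 − Φ(2.011)] = 0.044. Power = Φ(2.802 − 2.011) = Φ(0.791) = 0.785.

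Worked for R² = 0.10: 1/√0.90 = 1.054, and 1.960 × 1.054 = 2.066. Type I error = 2[1 − Φ(2.066)] = 0.039. Power = Φ(2.802 − 2.066) = Φ(0.736) = 0.769.

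| Assumed R² | True type I error | Power without strata |
|---|---|---|
| 0.02 | 0.048 | 79.4% |
| 0.05 | 0.044 | 78.5% |
| 0.10 | 0.039 | 76.9% |
| 0.20 | 0.028 | 72.9% |

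**If section 2.2.3 governs**

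No such miscalibration arises. A model with treatment and baseline score matches an unstratified allocation.

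**The case against.** The best defence is that little depends on this statistically. Under either scheme the comparison is randomised and the estimate unbiased, and the test is valid or slightly conservative. The choice of model covariates is also something that a statistical analysis plan, not shown here, commonly settles. Both points stand. They limit the seriousness of the finding and make the ANCOVA part a conditional consequence. They do not remove the conflict between two explicit statements: a fuller document could show which one is true, but the other would still be wrong.

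Section 2.4 also gives sex and age equality and inclusiveness as aims, which could describe the make-up of the sample. That reading is possible but weaker, for the reasons given in the comparison of the texts.

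Some stronger readings are tempting but not supported:

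- **Section 2.2.3 prescribes simple, coin-toss randomisation, so uneven splits within institutions should be expected.** The section says only that there are no stratification factors and that a computer program is used. Permuted blocks without strata would fit. The protocol gives no number of participants per institution, and strata by sex and age would not control splits within an institution.
- **The ANCOVA is wrong as it stands.** It is mismatched only if section 2.4 describes the true scheme.
- **The loss equals 5-10% of the sample, matching R².** That describes confidence-interval width. In terms of power the loss is smaller: (1.960 + 0.791)²/2.802² = 0.964 and (1.960 + 0.736)²/2.802² = 0.926, about 4% and 7% of the sample.

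**Conclusion.** The contradiction is established from the text alone and needs no assumption: one of the two stated allocation properties is wrong, and the sampling term in section 2.4 is wrong in any case. The ANCOVA mismatch is conditional on section 2.4 governing. Its effect is then conservative and modest: at R² of 5-10%, standard errors are overstated by 2.6-5.4%, with the type I error and power given for those values in the table. All of these sizes rest on the assumed R², alpha and power.

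This should be fixed, because the allocation method must be unambiguous and cannot be changed for participants already randomised. It does not threaten the validity of the treatment comparison.

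**What to change.** State one scheme in both sections before randomisation starts. The Introduction says that the pilot is still in preparation, so this costs little now.

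- **If allocation is stratified:** delete the parenthesis in section 2.2.3, call the method stratified randomisation in section 2.4, and define the age bands. Add sex and age to every between-group ANCOVA and to the imputation model. Cost: some wording, one setting in the randomisation program, and 2-3 degrees of freedom in each model. Both variables are already collected at baseline.
- **If allocation is unstratified:** delete the stratification claims in section 2.4, including the claim that the method limits confounding. The ANCOVA can stay as written. Prespecifying sex and age as covariates is then optional. Cost: wording only.

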**Figure 1 fig1:**
[figure not shown]
CONSORT flow diagram.

#### Sample size calculation

2.2.4.

In RCTs to calculate the sample size, four factors are required: significance level, power analysis, difference between groups, and standard deviation (SD; Charles et al., 2009). As there is only one RCT in Germany that applied the MCT-Silver, we chose to conduct a pilot study, and the sample size calculation for the RCT is calculated *a posteriori*. For the pilot study, we will include 32 participants, as 15–20 participants are needed to ensure the scientific validity of the results of a pilot study (Hertzog, 2008). The results of the pilot study will provide information on the above four factors as they are necessary for the calculation of the sample size.

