Metacognitive training for older adults with depression (MCT-Silver; Schneider et al., 2018; Bücker, 2019), is a cognitive-behavioral (CBT)-based group intervention, specifically designed for adults ages 60 years and older (all materials are available for free^1^). MCT-Silver aims to reduce the treatment gap by improving access to mental health care for the estimated 73% of older adults with depression who go untreated (Horackova et al., 2019). MCT-Silver is based on metacognitive training for psychosis (MCT; Moritz and Woodward, 2007) and metacognitive training for depression (D-MCT; Jelinek et al., 2015). Randomized controlled trials on D-MCT provide evidence for its efficacy on depressive symptoms (Jelinek et al., 2016), as well as metacognitive and negative cognitive beliefs (Hauschildt et al., 2022; Özgüç and Tanriverdi, 2022) at short- and intermediate follow-up intervals. Long-term efficacy of D-MCT remains equivocal (Jelinek et al., 2019). A pilot study examined the feasibility, acceptance, and effects of D-MCT as an add-on intervention in a group of older adults with depression who were completing an intensive inpatient treatment program (55+ years; *N* = 116). Per protocol analyses (*n* = 55) yielded a significant decrease in depressive symptoms (*d* = 1.06) and cognitive biases (*d* = 0.33). These results support the feasibility and acceptance of D-MCT among older adults with depression. A recently completed RCT in Germany, which compared MCT-Silver to an active control group (cognitive remediation; (Schneider et al., 2018)) yielded large and significant reductions on the primary outcome (Hamilton Depression Rating Scale) from baseline to post and 3-month follow-up (*d_MCT-Silver_* = 1.25 – 1.42; *d*_CR_ = 1.05 – 1.12). Group differences; however, did not reach significance (η_p_^2^ = 0.001 – 0.002). MCT-Silver yielded significant moderate to large effects compared to CR immediately following the intervention and after 3 months for self-reported depression (BDI-II: η_p_^2^ = 0.075 – 0.135) and rumination (RRS: η_p_^2^ = 0.087 – 0.127). A significant moderate effect was found for positive metacognitive beliefs (MCQ-PB) at post-assessment (η_p_^2^ = 0.067), but group differences did not reach significance at follow-up (η_p_^2^ = 0.027). Small reductions in negative cognitive beliefs (Dysfunctional Attitudes Scale-18B) at post- and at 3-month follow-up (*d_MCT-Silver_* = 0.24 – 0.30) were found for the MCT-Silver group, whereas negative cognitive beliefs were unchanged in the CR group (*d_CR_* = –0.06 – 0.06).

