
Like D-MCT, the main goal of MCT-Silver is to strengthen patients’ ability to reflect upon their thinking, and to recognize and correct their dysfunctional thought patterns and behavior (Moritz et al., 2018; Schneider et al., 2018) in order to ultimately reduce depressive symptoms. Additionally, MCT-Silver aims to increase awareness of depression-related information processing strategies, such as attentional preferences for negative information and mood-congruent memory (Blaney, 1986; Wittekind et al., 2014; McConnell and Troop-Gordon, 2021). Individual modules also address dysfunctional coping strategies (e.g., thought suppression, rumination) and metacognitive beliefs (e.g., rumination helps to solve problems). As a “modern” CBT-intervention, MCT-Silver includes third-wave elements drawn from acceptance and commitment therapy (Hayes et al., 2006) and imagery rescripting (Holmes et al., 2016). The training also addresses age-specific challenges and risk factors for depression in older adults (e.g., loneliness, functional limitations, loss of relationships).

MCT-Silver has not yet been validated for the Portuguese population and studies are needed to prove its efficacy in this population. Therefore, after the completion of a pilot study, a randomized controlled trial will be conducted to evaluate the efficacy of the intervention in older adults with depression. The research question of this study is as follows: “Does MCT-Silver in older adults with depression lead to a greater reduction in depressive symptoms and dysfunctional beliefs as well as improved metacognitive beliefs, quality of life, ruminative responses, self-esteem and attitudes towards aging compared to treatment as usual?.” The pilot study is in preparation. After completion of the pilot study and application of results as necessary (e.g., adjustment of MCT-Silver for the Portuguese population), we will continue with the intervention in order to finalise the RCT.

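### The plan looks to a 32-person pilot for all four sample-size inputs, but a pilot cannot supply significance level or power and is too small to fix the between-group difference

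*Protocol article*

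**What the plan says.** Section 2.2.4 (Sample size calculation) says that in an RCT "four factors are required: significance level, power analysis, difference between groups, and standard deviation". It notes that only one RCT of MCT-Silver exists and gives this as the reason for running a pilot first and calculating the RCT's size afterwards. On the pilot's size it says "For the pilot study, we will include 32 participants", with the justification that "15–20 participants are needed to ensure the scientific validity of the results of a pilot study". It closes by saying that "The results of the pilot study will provide information on the above four factors", because the calculation needs them.

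The section gives no significance level, power, target difference, SD or RCT sample size, and it names no source for them other than the pilot. The Introduction reports the earlier RCT's between-group result on BDI-II, which is this trial's primary outcome: "MCT-Silver yielded significant moderate to large effects compared to CR immediately following the intervention and after 3 months for self-reported depression" (partial eta squared 0.075 to 0.135). Section 2.2.4 does not use that result. The Introduction also says that the pilot is still being prepared.

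**The concern.** This is a stated procedure, not a detail left for a later document, and it goes wrong in two ways.

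- **Significance level and power are not pilot results.** They express how much risk of a false positive or a false negative the investigators accept. They must be chosen, whatever the pilot shows.
- **The between-group difference cannot be fixed by 32 people.** The reason given for the pilot's size is a general one about the validity of pilot studies. It says nothing about how precisely a difference between arms will be estimated.

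The SD is different: a pilot can reasonably inform it.

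The RCT's ability to answer its primary question is at stake. A pilot that overstates the effect by chance leads to an RCT that is too small. One that understates it leads to an RCT that looks unaffordable or cannot be sized at all. Once recruitment has ended, the analysis cannot repair a trial of the wrong size.

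**Working it through.** The plan states no RCT sample size, so there is no figure to reproduce. The check asks how well a pilot of this size could determine the difference, and what would follow if the RCT were sized on it.

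**Inputs**

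- Pilot of 32 participants (section 2.2.4). The split is not stated; 16 per arm is assumed. Unequal arms or attrition would make matters worse.
- Partial eta squared of 0.075 to 0.135 on BDI-II (Introduction), used only to choose an illustrative true effect.
- Two-sided 0.05, 80% power, equal arms, no dropout and no clustering by therapy group. All are assumptions, since the article gives no values.

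**Step 1. Illustrative effect.** For two equal groups, d = 2·√(η²/(1 − η²)).

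- η² = 0.075: d = 2·√(0.075/0.925) = 0.57
- η² = 0.135: d = 2·√(0.135/0.865) = 0.79

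**Step 2. Precision of the pilot's d.** SE(d) = √(2/16 + d²/64).

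- d = 0.57: √(0.125 + 0.0051) = 0.36, so the 95% interval is about ±1.96 × 0.36 = ±0.71.
- Exact noncentral-t interval for an observed d of 0.50: −0.21 to 1.20.

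**Step 3. RCT size for a given d.** n per arm = 2·(1.960 + 0.842)²/d² = 15.70/d².

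- d = 0.57: 15.70/0.325 = 48.3, so 49 per arm (50 by noncentral t).
- d = 0.79: 15.70/0.624 = 25.2, so 26 per arm (27 by noncentral t).
- Observed d = 0.50: 63 per arm at the point estimate, 11 per arm at the upper 95% limit, and undefined at the lower limit, which is below zero.

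**Step 4. Sizing the RCT on the observed effect, true d = 0.57.** Pilots with 16 per arm were simulated, and each RCT was sized from that pilot's d.

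- 10th to 90th percentile of the pilot's d: 0.12 to about 1.06.
- About 9% of pilots give d of 0.1 or less.
- Among the other 91%, the 10th to 90th percentile of RCT size is about 15 to 250 per arm. This is a percentile range, not the extremes.
- In that group, about 55% of RCTs have real power below 80%, and 26–27% below 50%.

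One case by hand: a pilot d of 1.06 gives 15.70/1.124 = 14.0, so about 15 per arm with the t correction. If the true d is 0.57, real power is about Φ(0.57·√(15/2) − 1.96) = Φ(−0.40), or about 34%.

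**Step 5. Sensitivity to the true effect.** In this table an RCT is sized whenever the pilot's d is above zero, so the row for 0.57 differs a little from step 4.

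| True d | Pilots with d ≤ 0 | RCT n per arm, 10th–90th percentile | Below 80% power | Below 50% power |
|---|---|---|---|---|
| 0.50 | 8% | 16–570 | 54% | 30% |
| 0.57 | 5% | 14–385 | 52% | 26% |
| 0.79 | 1% | 10–122 | 49% | 19% |

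**Step 6. The SD, for contrast.** With 30 degrees of freedom, the 95% limits for the SD are 0.80 to 1.34 times the estimate, and the one-sided 80% upper limit is 1.13 times it. That is precise enough to be useful.

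**The case against.** **The wording is loose.** To say that the pilot provides information on the factors is not to say that its point estimate will be put into the formula. A fuller protocol might use a confidence limit or a minimally important difference. This stands as a caution, which is why the power figures above are conditional on sizing from the observed effect. It does not remove the problem: the section names no other source for the difference, and under any reading a pilot cannot inform significance level or power.

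**Part of it may be careless drafting, and no number is locked in.** This is fair. It makes the correction cheap, but the sentence as written still describes a wrong procedure.

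**The earlier RCT is no safe substitute.** A reader might infer that its BDI-II effect is plainly a better basis than the pilot. The article does not support that. BDI-II was not that trial's primary outcome, and the primary outcome showed no significant group difference (partial eta squared 0.001 to 0.002). The comparator was active rather than treatment as usual, and the article does not give that RCT's sample size, so its precision cannot be judged. The authors' caution about relying on one RCT is reasonable. The effect can serve as context only.

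**Pooling.** The Introduction says "we will continue with the intervention in order to finalise the RCT" after the pilot. A reader might infer that pilot participants will enter the RCT analysis and that the type I error would then be inflated. The article does not say so. It describes a completed pilot, possible adaptation of the intervention, and then an RCT. That inference forms no part of this point.

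**Baseline adjustment.** The planned ANCOVA would reduce the residual SD, but a standardised effect estimated from 32 people remains imprecise.

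**Conclusion.** The point holds in this form: section 2.2.4 assigns to a 32-person pilot two inputs that no pilot can supply and a third that this pilot cannot usefully estimate. The first part needs no calculation. The second rests on a standard error for d of about 0.36, which assumes 16 per arm.

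The consequence for the RCT is conditional. If the observed effect were used, then for true effects of 0.50 to 0.79 roughly half or more of the resulting RCTs would fall short of 80% power, and about a fifth to a third would have less than 50%. These figures assume two-sided 0.05, 80% power, no dropout and no clustering. They illustrate the method's instability and do not recommend a sample size. Using the pilot for the SD is sound. The text should be corrected before the pilot's results are known, because a target difference chosen afterwards can no longer be shown to be independent of them.

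**What to change.** Revise section 2.2.4 as follows:

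1. State significance level and power now, as design choices.
2. Fix the target between-group difference on BDI-II in advance, from a justified minimally important difference. Cite the earlier RCT's effect (d of about 0.57 to 0.79) as context only, noting its active comparator and that BDI-II was not its primary outcome.
3. Limit the pilot's role to the SD, attrition and feasibility. Take the SD with a margin, for example the one-sided 80% upper limit, which is 1.13 times the estimate if all 32 participants contribute.
4. Say that the pilot's observed difference will not set the target difference.

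The cost is a change of wording before the RCT starts. The investigators give up the option of a smaller RCT after a favourable pilot, and a cautious SD will make the trial somewhat larger.
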